### Recruitment and randomization

In Pakistan, no official sampling frame of textile mills is available but several business and textile associations represent the country’s textile mills and from them we will acquire a list of industrial plants in Karachi. To be eligible, textile mills will need to: (1) be from the formal sector and registered with business associations and the Government Labor Department; (2) have either spinning or weaving sections, or both; (3) employ at least 50 eligible workers in their spinning and weaving sections; (4) have a workforce in which at least 75% of staff have been employed for 12 months or longer; (5) have a management willing to participate in the planning and implementation of the study and (6) have no plans to introduce major improvements over the next 2 years.

Eligible workers at each mill will be identified by the Human Resources Department. We will include male textile workers aged ≥ 18 years who are employed in the bale-opening, blowing, carding, spinning, twisting, winding, warping, weaving or waste recycling sections. In Pakistan, women very rarely work in these sections and we will not include them. Those who do not give consent will be excluded. We will also exclude workers from the wet-processing areas (dyeing or bleaching), stitching and packaging sections, as well as support or administrative staff. At each mill, personal air sampling will be done on five purposively selected workers (100–150 in all) representing the range of sections and jobs. For this purpose, the latter will be categorized into one of four groups: (1) helpers, cleaners and doffers; (2) machine operators; (3) jobbers and fitters and (4) masters, in-charge or supervisors.

We will purposively select 28 textile mills and assign them equally to the intervention or the control arm by stratified randomization. Stratification will be according to the total number of employees at the mill (≤ 250/> 250) and occupational health and safety measures in place at baseline (as assessed by a walk-through survey and categorized as good or poor). Within strata, allocation to intervention or control will be through random numbers generated at Imperial College London and shared with the research team in Pakistan. Blinding of mill staff will not be possible but we will “blind” the data collection team including the technicians measuring dust levels, and the laboratory personnel involved in weighing filters for gravimetric analysis.

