### Statistical analysis

Data will be entered through Epi Data and analyzed with STATA. Frequency counts will be derived for baseline socio-demographic variables and respiratory symptoms (categorical variables). Measures of central tendency and dispersion will be reported for continuous variables (cotton-dust levels and lung function indices). Correlations between the cotton-dust levels and lung function (FEV_1_, FVC and FEV_1_/FVC ratio) will be assessed through Pearson’s correlation coefficient.

Models based on generalized estimating equations (GEEs) will be developed to determine changes in the cotton-dust levels, frequency of respiratory symptoms, FEV_1_ (lung function indices) and respiratory sickness absenteeism. The changes in these outcome variables from baseline will be compared between the intervention and control groups. The GEE models will take into account the clustering by mills, as well as the correlation between repeated measures. Multicollinearity will be assessed between covariates and will be taken into account in the multivariable models.

We will analyze by intention to treat, and workers will be classified according to their assigned treatment group at the time of randomization. Sensitivity analyses will be performed to explore the potential impact of losses to follow-up.

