### Statistical power

Based on previous occupational trials, we assumed that the intra-class correlation coefficients for the outcome measures were 0.02 [29, 30].

For cotton-dust levels: assuming the level of significance at 5%, power 80% and a 15% or 0.65 mg/m^3^ difference in mean PM levels in the intervention arm compared to the control arm (expected mean dust level in control arm: 0.6 with a standard deviation of 2.5); the sample size required without clustering is 233/arm. The variance inflation factor is:
$$ \left[1+\left(50-1\right)\ast 0.02\right)\Big]=1.98, $$

so the sample size is inflated to 461, which rounds up to 10 groups of 50 in each arm – which increases to 10 groups of 61 in each arm after inflating for losses (* 1.05 * 1.05 * 1.1 = * 1.212).

For respiratory symptoms: the trial is powered to detect a difference of 10% in the proportion of workers reporting respiratory symptoms between the intervention and control arms. Assuming a level of significance at 5%, power 80%, the proportion of workers having respiratory symptoms at the baseline as 40%; without clustering we would require 354/arm. With clustering, the new sample size is 701/arm which – in groups of 50 – means 14 groups of 50 in each arm of the study. Inflating these numbers for losses gives 14 groups of 61.

For lung function: assuming level of significance at 5%, power 80%, 5% or a 150-ml difference in mean FEV_1_ (standard deviation 31) in the intervention arm compared to the control arm (expected mean FEV_1_ in control arm: 3279 ml, standard deviation 690); the requirement without clustering would be 333 per arm, which inflates to 660 with clustering, which again leads to 14 groups of 50 in each arm and this again inflates to 14 groups of 61 after inflating for losses.

Based on the above calculation, we intend to recruit 854 workers from 14 clusters in each arm, a total of 1708 participants in 28 clusters.

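### The sample size makes no allowance for having only 28 mills: with a t reference on 26 df, power is about 77% for symptoms, and the GEE analysis needs a stated small-sample correction

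*Protocol article*

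**What the plan says.** The Statistical analysis section of the protocol article commits the outcomes to GEE: "Models based on generalized estimating equations (GEEs) will be developed to determine changes in the cotton-dust levels, frequency of respiratory symptoms", together with FEV1 and respiratory sickness absence. On dependence it says that "The GEE models will take into account the clustering by mills, as well as the correlation between repeated measures". On software it says "Data will be entered through Epi Data and analyzed with STATA". It names no variance estimator, working correlation, reference distribution or small-sample correction, and it excludes none.

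The Statistical power section gives an explicit calculation for dust, symptoms and FEV1 at 5% significance and 80% power. On clustering, "we assumed that the intra-class correlation coefficients for the outcome measures were 0.02", which with 50 workers per mill gives a variance inflation factor of 1.98. Symptoms and FEV1 each lead to 14 mills of 50 per arm. After inflation for losses, "we intend to recruit 854 workers from 14 clusters in each arm, a total of 1708 participants in 28 clusters".

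The Study design section makes the mill the unit of randomization. The Recruitment and randomization section defines four strata: "Stratification will be according to the total number of employees at the mill (≤ 250/> 250) and occupational health and safety measures in place", the latter graded good or poor.

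**The concern.** When mills are randomized, evidence on the treatment effect accumulates over mills. With 28 mills and two arms, 26 degrees of freedom remain for between-mill variation. This matters in two places.

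- **Power.** A normal-quantile formula times a design effect treats the variance as known. If the analysis then holds its size at 5%, it uses a wider critical value and has less power than the formula promises. The article prints this calculation and fixes the number of mills from it, so this is a point about stated content.
- **Test size.** The usual robust (sandwich) variance for GEE is a large-sample quantity in the number of clusters. With 14 per arm it is biased downwards, and a z reference adds to the problem. Without a correction, p-values and intervals for the primary outcomes would be somewhat too favourable.

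**Working it through.** **Inputs (Statistical power section).** ICC 0.02; 50 analysed workers per mill; 14 mills per arm. Symptoms: 40% and a 10-point difference, taken as 40% v 30%. FEV1: 150 ml, SD 690 ml (the SD that reproduces the stated number). Dust: 0.65 mg/m³, SD 2.5. Sidedness is not stated; two-sided reproduces the figures.

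**Step 1: reproduce the plan's figures.** Per arm, n = (1.960 + 0.842)² × V / δ², where V is the sum of the two arms' variances. The design effect is 1 + 49 × 0.02 = 1.98.

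- Dust: V = 2 × 2.5², n = 232.2, so 233; × 1.98 = 461.3 (stated 461).
- Symptoms: V = 0.4 × 0.6 + 0.3 × 0.7 = 0.45, n = 353.2, so 354; × 1.98 = 700.9 (stated 701).
- FEV1: V = 2 × 690², n = 332.2, so 333; × 1.98 = 659.3 (stated 660).

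All three agree, using normal quantiles with no degrees-of-freedom term and no added mills.

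**Step 2: power with a t reference.** At 14 × 50 = 700 per arm, λ = δ / √(V × 1.98 / 700). Power is taken from the normal distribution, then from the noncentral t on 28 − 2 = 26 df, then on 23 df (arm plus four strata).

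| Outcome | λ | z | t, 26 df | t, 23 df |
|---|---|---|---|---|
| Symptoms | 0.10 / 0.03568 = 2.803 | 80.0% | 77.0% | 76.6% |
| FEV1 | 150 / 51.90 = 2.890 | 82.4% | 79.5% | 79.0% |
| Dust | 0.65 / 0.1880 = 3.457 | 93.3% | 91.4% | 91.1% |

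On the t basis, symptoms reach 79.97% with 15 mills of 50 per arm and 82.6% with 16. FEV1 reaches 82.3% with 15. If all 61 recruits per mill were analysed, the 26-df power would be 80.7% for symptoms and 83.0% for FEV1. However, the step from 50 to 61 is the plan's own allowance for losses (1.05 × 1.05 × 1.1 = 1.213), so it cannot also serve as a margin here.

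**Step 3: size of an uncorrected GEE test, if that were used.** With equal mills, the uncorrected sandwich variance is 13/14 of its unbiased value on average. √(13/14) = 0.964, so standard errors are about 3.6% too small. The size is P(|t26| > 1.960 × 0.964) = P(|t26| > 1.889) = 7.0%. Even an unbiased variance read against z gives P(|t26| > 1.960) = 6.1%.

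Simulation (40,000 trials per scenario; continuous and binary outcomes; ICC 0.02 and 0.05; mill-size coefficient of variation 0, 0.4 and 0.7) gave:

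- uncorrected variance, z: 6.9% to 7.5%
- variance multiplied by 28/27, z: 6.4% to 7.0%
- Mancl-DeRouen variance, z: 5.1% to 5.5%
- Kauermann-Carroll variance, t on 26 df: 4.9% to 5.3%

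**Step 4: cost in interval width.** The t critical value on 26 df is 2.056. Relative to uncorrected z, intervals widen by (2.056 / 1.960) × √(14/13) = 1.088, about 9%.

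**The case against.** The strongest objection is that the uncorrected test is nowhere in the document. The article says GEE in Stata and no more. The variance option and reference distribution are details that an article commonly leaves to a full protocol or analysis plan, and neither is shown. This stands. A reader might infer that every primary p-value and interval in this trial will be too favourable. The text does not support that, because it neither commits to uncorrected inference nor excludes a correction.

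A reader might also infer that adjustment will push the error rate higher still. A mill-level analogue with four stratum terms and assumed stratum sizes of 8, 8, 6 and 6 gave about 9% uncorrected. But the article names no mill-level covariate and does not say that the stratification factors enter the model, so this too is hypothetical.

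On power, the objection is that 77% is not the power of the planned analysis. The plan compares changes from baseline using repeated measures, while the calculation sizes a single comparison. No baseline-to-follow-up correlation r is given. Taking r as an assumption, 26-df power for symptoms with baseline adjustment (λ / √(1 − r²)) is 77% at r = 0, 81% at 0.3 and 88% at 0.5. With plain change scores (λ / √(2(1 − r))) it is 63% at r = 0.3, 77% at 0.5 and 94% at 0.7. The ICC matters more than the reference distribution: the design effect is 1.49 at ICC 0.01 and 2.47 at 0.03, and power is then 87.5% and 68%. This also stands. It limits what the 77% means, but it does not rescue the printed 80%, which claims no gain from baseline data and rests on the same ICC.

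**Conclusion.** The point holds in a limited form. The published calculation ignores the small number of mills. On its own inputs, a test that controls its size on 26 df delivers 77.0% for symptoms and 79.5% for FEV1. That is 3 points and half a point below the stated 80%. The symptoms shortfall matters most because that outcome sets the number of mills and leaves no slack: 14 × 50 = 700 against 701 required. Dust is not short at 14 mills on the 50-per-mill premise, although personal sampling covers only five workers per mill, so that figure does not describe the personal-exposure outcome.

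The type I error of about 7% is correct for an uncorrected robust variance with z tests at 14 mills per arm, and is a risk to close off rather than an error in the text. The power figures assume a two-sided test, 40% v 30%, ICC 0.02, equal mills of 50 and a simple follow-up comparison. The matter is worth correcting because the remedy is cheap, but it does not threaten the trial.

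**What to change.** - Keep GEE with the mill as the cluster. State one small-sample-corrected variance, for example Kauermann-Carroll, with a t reference on the number of mills minus the number of mill-level parameters: 26 df with arm alone, fewer if stratification terms enter. Fix this before outcome data are seen.
- Restate power in the Statistical power section on the same basis: about 77% for symptoms and 79% for FEV1 (79.5% on 26 df, 79.0% on 23 df). Say that these figures are for a simple follow-up comparison and that baseline adjustment may recover some power. If 80% is to be kept on the t basis without such a gain, the inputs imply 16 mills of 50 per arm for symptoms (15 falls just short) and 15 for FEV1.

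Without added mills, the cost is wording and minor programming, intervals about 9% wider than under uncorrected z, and a stated power between half a point and 3 points below 80%.

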### Statistical power

Based on previous occupational trials, we assumed that the intra-class correlation coefficients for the outcome measures were 0.02 [29, 30].

For cotton-dust levels: assuming the level of significance at 5%, power 80% and a 15% or 0.65 mg/m^3^ difference in mean PM levels in the intervention arm compared to the control arm (expected mean dust level in control arm: 0.6 with a standard deviation of 2.5); the sample size required without clustering is 233/arm. The variance inflation factor is:
$$ \left[1+\left(50-1\right)\ast 0.02\right)\Big]=1.98, $$

so the sample size is inflated to 461, which rounds up to 10 groups of 50 in each arm – which increases to 10 groups of 61 in each arm after inflating for losses (* 1.05 * 1.05 * 1.1 = * 1.212).

For respiratory symptoms: the trial is powered to detect a difference of 10% in the proportion of workers reporting respiratory symptoms between the intervention and control arms. Assuming a level of significance at 5%, power 80%, the proportion of workers having respiratory symptoms at the baseline as 40%; without clustering we would require 354/arm. With clustering, the new sample size is 701/arm which – in groups of 50 – means 14 groups of 50 in each arm of the study. Inflating these numbers for losses gives 14 groups of 61.

For lung function: assuming level of significance at 5%, power 80%, 5% or a 150-ml difference in mean FEV_1_ (standard deviation 31) in the intervention arm compared to the control arm (expected mean FEV_1_ in control arm: 3279 ml, standard deviation 690); the requirement without clustering would be 333 per arm, which inflates to 660 with clustering, which again leads to 14 groups of 50 in each arm and this again inflates to 14 groups of 61 after inflating for losses.

Based on the above calculation, we intend to recruit 854 workers from 14 clusters in each arm, a total of 1708 participants in 28 clusters.

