### Study outcomes

The primary outcomes of the trial at 18 months post intervention, will be: (1) personal dust exposure levels (in mg/m^3^), and their change from baseline, in the intervention as compared with the control arm; (2) dust levels in different sections of the mill (in mg/m^3^), and their changes from baseline, in the intervention as compared with the control arm; (3) changes from baseline in the prevalence of respiratory symptoms, in the intervention as compared with the control arm (a composite variable will be used for presence of one or more respiratory symptoms including; cough, sputum, wheeze, shortness of breath and chest tightness) and (4) changes in FEV_1_ from baseline to follow-up, in the intervention as compared with the control arm.

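### Dust is framed as an absolute difference in arithmetic means although the target is also a percentage; a log-scale ratio would be modestly more precise, once the control mean is reconciled

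*Protocol article*

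**What the plan says.** Protocol article, Study outcomes: the first primary outcome is "personal dust exposure levels (in mg/m^3^), and their change from baseline", compared between arms at 18 months. The second is the dust level in mill sections, in the same unit and also with its change from baseline.

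Protocol article, Statistical power: the target for dust, given both as 15% and as 0.65 mg/m³, is a "difference in mean PM levels in the intervention arm compared to the control arm", with "expected mean dust level in control arm: 0.6 with a standard deviation of 2.5". From this, "the sample size required without clustering is 233/arm", and after the design effect of 1.98, "so the sample size is inflated to 461, which rounds up to 10 groups of 50 in each arm".

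Protocol article, Recruitment and randomization: personal air sampling covers five workers per mill, so about 70 per arm with 14 mills.

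Protocol article, Statistical analysis: GEE models will compare changes in dust between arms. No link, distribution or transformation is given. No log scale, ratio or geometric mean for dust appears anywhere in the article.

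**The concern.** A concentration has a floor at zero and usually a long upper tail. When the SD is large relative to the mean, a few high readings carry much of an arithmetic mean, and an absolute change gives the dustiest mills more weight than the cleaner ones. The protocol also states its target as a percentage, and the earlier farm trial that it cites in the Background is reported as a reduction of about 25%. A proportional question is therefore framed on an absolute scale.

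At stake is some precision on a primary outcome that rests on only about 70 personal readings per arm. The choice of scale should also be fixed before the data are seen. For section dust there is a further reason: particle counts are converted to cotton dust through a calibration factor from a small number of sites, and in mg/m³ any error in that factor scales the estimated effect directly.

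**Working it through.** **Inputs.** From Statistical power: difference 0.65 mg/m³ or 15%, SD 2.5, control mean 0.6, alpha 5% (two-sided reproduces the stated figure), power 80%, ICC 0.02, design effect 1.98. From Recruitment and randomization: 14 mills per arm, five personal samples each. Assumption not in the documents: dust is lognormal, and the intervention multiplies it by 0.85.

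**1. Reproduce the stated size.** With (1.960 + 0.842)² = 7.849:

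n = 2 × 7.849 × 2.5² / 0.65² = 232.2, so 233 per arm; 233 × 1.98 = 461.

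Both stated figures reproduce, and only from the arithmetic contrast. The control mean does not enter the formula.

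**2. Check the control mean.** 0.65 / 0.6 = 1.08, so the stated difference is 108% of the printed mean and the intervention mean would be −0.05. Conversely 15% = 0.65 implies a mean of 0.65 / 0.15 = 4.33. The printed mean and the stated effect cannot both hold.

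**3. Skew at the implied mean.** CV = 2.5 / 4.33 = 0.577. Lognormal skewness = (CV² + 3) × CV = 1.9, which is moderate.

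**4. Log-scale requirement at 4.33.** Log variance = ln(1 + 0.577²) = 0.287, so the log SD is 0.536. ln(0.85) = −0.1625.

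n = 2 × 7.849 × 0.287 / 0.1625² = 171 per arm, unclustered.

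**5. Like-for-like raw requirement.** The 233 uses SD 2.5 in both arms. Under a proportional effect the intervention SD falls to 0.85 × 2.5 = 2.125, with variance 4.516:

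n = 7.849 × (6.25 + 4.516) / 0.65² = 200 per arm.

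The saving is 1 − 171/200, about 15%. Against 233 it looks like 27%, but part of that gap comes only from the equal-SD assumption.

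**6. Power with five samples per mill.** Design effect 1 + 4 × 0.02 = 1.08; effective n = 70 / 1.08 = 64.8 per arm; t test on mill means, 26 df.

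- Log: SE = 0.536 × √(2/64.8) = 0.0942; effect/SE = 0.1625/0.0942 = 1.73; power about 38%.
- Raw: SE = √(10.766/64.8) = 0.408; effect/SE = 0.65/0.408 = 1.60; power about 34%.

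Simulation of the same design gives the same figures to within about one point.

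**7. Sensitivity to the control mean.** SD 2.5, 15% reduction, unclustered n per arm. The like-for-like raw figure is the equal-SD figure × (1 + 0.85²)/2 = 0.861.

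| Control mean | Log | Raw, equal SD | Raw, like for like | Saving, like for like |
|---|---|---|---|---|
| 4.33 (implied) | 171 | 233 | 200 | 15% |
| 2.5 (intermediate) | 412 | 698 | 601 | 31% |
| 0.6 (printed) | 1,730 | 12,113 | 10,432 | 83% |

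The log scale needs fewer workers at each mean, and the advantage grows as the mean falls relative to the SD.

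**The case against.** The strongest objection is that nothing binding has been fixed. The mean difference stands only in the sample-size paragraph, the outcome definition gives a unit but no summary measure, and the GEE text would accommodate a log link or log dust. A condensed article commonly leaves that choice to the full protocol or analysis plan. This stands in part. It is not established that the final analysis will lose precision, and the silence on link and transformation is no fault. But everything that is written (unit, change from baseline, effect and SD) points to the absolute contrast, and that wording would need aligning even if a plan not shown uses logs.

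A reader might infer strong skew from the printed figures: with mean 0.6 and SD 2.5, a normal distribution would put Φ(−0.24) = 41% of readings below zero, and the log scale would then gain far more. The documents do not support this. A mean of 0.6 cannot coexist with 15% = 0.65, so the pair is evidence of a reporting error before it is evidence about the distribution of dust.

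It is also fair that a ratio of geometric means answers a different question from a difference in arithmetic means, and that mg/m³ serves a stated purpose, namely comparison with cotton-dust standards (Discussion). Back-transformed values meet that need. For section dust the article gives no mean or SD, so no gain can be quantified there.

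Finally, scale is not the main power problem for personal dust. That stands: power is far below 80% on either scale.

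**Conclusion.** The point holds in a limited form. The stated outcome and effect wording for dust points to an absolute contrast of arithmetic means, while the target is also proportional and the quantity cannot be negative. At the implied mean of 4.33 the gain from a log-scale analysis is modest: about 15% fewer workers like for like, and about four percentage points of power at the 15% target with five samples per mill. It would be larger if the true mean is lower relative to the SD.

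These sizes rest on a lognormal shape, a proportional effect, SD 2.5 and ICC 0.02. The loss is conditional, because the GEE scale is open. The contradiction between the control mean and the effect is the more basic matter and comes first.

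**What to change.** 1. Reconcile the control mean of 0.6 with the 15% and 0.65 mg/m³ target in Statistical power, giving the source of the mean and SD.
2. Define the personal dust outcome as log concentration. Report the 18-month ratio of geometric means, intervention to control, with baseline log dust as a covariate, within a model that keeps the clustering by mill. State the target as a ratio of 0.85.
3. Show back-transformed concentrations in mg/m³ by arm, for comparison with dust standards.
4. Use the same scale for section dust, where a constant multiplicative calibration factor cancels from the ratio. Note that the article gives no mean or SD for this outcome.

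The cost is wording and a restated effect measure, with no added fieldwork. The small downside is that the headline result is a ratio and not an absolute difference. The change does not address the gap between five sampled workers per mill and the 50 assumed in the calculation, which needs its own correction.

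### The dust planning figures cannot all be true: 15% of a control mean of 0.6 is 0.09 mg/m³, not 0.65, although the stated sample size does follow from 0.65 and an SD of 2.5

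*Protocol article*

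**What the plan says.** All the dust planning inputs stand in one sentence of the protocol article, section Statistical power. The target is "a 15% or 0.65 mg/m^3^ difference in mean PM levels in the intervention arm compared to the control arm", at 5% significance and 80% power. In brackets comes the "expected mean dust level in control arm: 0.6 with a standard deviation of 2.5". From these the article concludes that "the sample size required without clustering is 233/arm". It then applies a variance inflation factor of 1.98, from groups of 50 and an intra-class correlation of 0.02: "so the sample size is inflated to 461, which rounds up to 10 groups of 50 in each arm". After allowance for losses this becomes 10 groups of 61.

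Two other sections bear on the point. Study outcomes lists personal dust exposure and dust levels by mill section, both in mg/m³, as the first two primary outcomes. Background says that the intervention is meant to reduce dust, so the planned difference is a fall.

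**The concern.** The sentence treats 15% and 0.65 mg/m³ as the same effect and then gives a control mean at which they differ about sevenfold. At that mean the absolute target exceeds the whole of the expected exposure, so the intervention arm would need a negative dust concentration to meet it.

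What is at stake is the claim of 80% power for a primary outcome. If the absolute difference is right and the mean is misprinted, the claim stands on its own terms. If the mean is right, the trial has almost no power for a 15% reduction, and the difference it was sized on cannot occur. Without a correction, a null dust result could not be read against a planning effect known to be attainable.

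**Working it through.** **Inputs** (protocol article, Statistical power): significance level 5%, power 80%, difference given as 15% and as 0.65 mg/m³, control mean 0.6, SD 2.5, intra-class correlation 0.02, groups of 50. Two assumptions: the test is two-sided (not stated, but only this reproduces the figure), and 0.6 is in mg/m³ (no unit is printed beside it).

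**1. Reproduce the stated figure.** For two means with equal allocation, n per arm = 2 (z₀.₉₇₅ + z₀.₈₀)² SD² / d².
- z₀.₉₇₅ + z₀.₈₀ = 2.8016, and its square is 7.849.
- With d = 0.65 and SD = 2.5: 2 × 7.849 × 6.25 / 0.4225 = 232.2, rounded up to 233. This matches.
- A one-sided test gives 183, which does not match.
- Design effect: 1 + 49 × 0.02 = 1.98, and 233 × 1.98 = 461.3, stated as 461. This matches.

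The control mean does not enter the formula. The calculation used 0.65 and 2.5.

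**2. Check the three effect figures in pairs.**
- Keep 15% and the mean of 0.6: d = 0.15 × 0.6 = 0.09 mg/m³, and 0.65 / 0.09 = 7.2.
- Keep 0.65 and the mean of 0.6: 0.65 / 0.6 = 108% of the control mean, and 0.6 - 0.65 = -0.05 mg/m³, which is impossible.
- Keep 15% and 0.65: control mean = 0.65 / 0.15 = 4.33 mg/m³, a value that the article does not give.

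**3. What each possible reading does to n and power** (SD 2.5 kept throughout).
- Mean about 4.33, difference 0.65: n stays at 233 per arm, or 461 with clustering.
- Mean 0.6, difference 0.09: n = 2 × 7.849 × 6.25 / 0.0081 = 12,112.5, so 12,113 per arm before clustering. With clustering, 12,113 × 1.98 ≈ 23,984 per arm, about 480 groups of 50.
- Power for 0.09 with 14 groups of 50 measured per arm: effective n = 700 / 1.98 = 353.5, standard error = 2.5 × √(2 / 353.5) = 0.188, and 0.09 / 0.188 = 0.479. Power = Φ(0.479 - 1.960) + Φ(-0.479 - 1.960) = 0.069 + 0.007 = 0.077, about 8%. Counting only rejections in the intended direction, it is about 7%.

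**4. Does the trial's total depend on this?** Dust asks for 10 groups per arm. The same section derives 14 groups of 61 per arm from respiratory symptoms (701 per arm) and from FEV₁ (660 per arm). 14 × 61 = 854 per arm, and 2 × 854 = 1708.

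**The case against.** The strongest reply is that 0.6 is a misprint and nothing follows from it. The control mean plays no part in a two-means calculation, 233 and 461 come out as printed, and a mean near 4.33 would reconcile the percentage with the absolute difference at no cost to n. Much of this stands. A reader might infer that the dust sample size has no valid basis, or that it is impossible to tell whether the trial was sized on 0.09 or 0.65. The article supports neither inference: 0.65 is printed, 233 follows from it, and 0.09 would have given 12,113.

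The reply does not remove the error. Nothing in the article gives or implies a mean of 4.33, so the misprint remains an assumption. The sentence is wrong as written, and no other section corrects it.

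Two further inferences are tempting and should not be drawn. One is that an SD of 2.5 around a mean of 0.6 proves a figure wrong because a normal distribution would then extend far below zero. Dust exposure cannot be negative and may be strongly skewed, and the article does not say that individual values are normal, so the ratio invites a query and no more. The other is that 0.6 and 2.5 are a geometric mean and geometric SD. Nothing in the text suggests this, and it would not make 15% equal 0.65.

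**Conclusion.** The point holds as an internal contradiction in the stated effect for a primary outcome: 15%, 0.65 mg/m³ and a control mean of 0.6 cannot all be correct. The calculation itself is sound for a difference of 0.65 and an SD of 2.5. What is unsettled is whether 0.65 is 15% of the expected mean, and so whether it is an attainable target.

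The size depends on which figure is wrong. If the mean is about 4.33 mg/m³, one number changes and 233 and 461 stand. If the mean is 0.6, the claim of 80% power for a 15% reduction fails, with power of about 8% under the article's own clustering assumptions and 14 × 50 measured workers per arm. That figure assumes a simple two-sided comparison of means at one time point with SD 2.5, and 50 dust measurements per mill, as the calculation supposes. How many workers per mill are in fact sampled for dust is a separate matter and is not relied on here.

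A reader might also infer that recruitment has to change. It does not: the 28 mills and 1708 workers come from the symptom and FEV₁ calculations.

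**What to change.** Check the control mean, SD, absolute difference and percentage against the source of the planning data and against the baseline dust survey, which precedes randomization. Restate them in Statistical power so that they agree, with units and source.
- If the control mean is about 4.33 mg/m³, replace the 0.6 and leave 233 and 461 as they are.
- If the control mean is 0.6, withdraw the claim of 80% power for a 15% reduction and state what difference the planned dust measurements can detect.

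In either case, say that the dust calculation does not set the number of mills. A change of outcome scale or analysis model is not needed to repair this error. The cost is one corrected paragraph and, in the second case, one recalculation. Recruitment is not affected.
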